**Figure 3 F3:**
[figure not shown]
**measurements of study 2.** Note: *self-rated **observer rated ***interview.

### Intervention

Investigational treatment will be STEPPS, as described in the introduction, added to individual TAU (Treatment As Usual) for BD. According to current guidelines for treatment in BD
[18] TAU consists of three necessary modules: pharmacotherapy, information and psycho-education, and interventions to improve self-management.

### Sample size

Inclusion of 64 patients for each group has a power of 80% and an alpha of 5% to detect an average difference in Cohen’s d (0.50). Assuming a loss of 10% 140 patients will be enrolled. Patients will participate in STEPPS groups that are normally organized in the participating centers, i.e., there are no groups exclusively set up for this research population. The rationale is that in clinical practice, patients with BD and comorbid borderline personality features will be treated in routinely organized STEPPS groups, together with patients with a primary diagnosis of BPD.

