[18]). There clearly is a need to develop new psychotherapies or evaluate existing psychological interventions to improve the course of BD and quality of life as well as reducing mental health care utilization in these patients. This study evaluates the addition of STEPPS (Systems Training for Emotional Predictability and Problem Solving) to treatment as usual (TAU) in patients with BD and comorbid BPD or borderline personality features as described in the inclusion criteria. STEPPS is a cognitive behavioral skills group treatment for BPD developed to improve their emotion regulation. The training consists of 20 weekly sessions of approximately 2,5 hours and has 4 parts: psycho-education, emotion regulation skills, behavioral skills, and emotion handling plan. Two trainers deliver the training. The group size is 8–12 patients. An uncontrolled pilot study presented an indication of the effectiveness of the STEPPS in BPD
[19]. A randomized trial
[20] showed that BPD patients treated with STEPPS compared with TAU showed larger reduction of BPD symptoms, more quality of life and less general psychological symptoms. All improvements were still significant after 6 months. In another randomized trial
[21] STEPPS plus TAU also led to greater improvements in impulsivity, negative affectivity, mood, and global functioning. STEPPS is included in the Dutch guidelines for treatment in BPD
[22]. The underlying assumption is that BPD is characterized by a defect in the individual’s internal ability to regulate emotional intensity. The aim of the training is to gain skills to manage emotions and behavior related problems. Friends and family members provide the “reinforcement team” and learn to reinforce and support newly learned skills of the patients (http://www.steppsforbpd.com).

BPD can be conceptualized as a dimensional or spectrum disorder. Patients may suffer from significant symptoms of BPD without meeting the full diagnostic criteria defined by DSM-IV-TR. To increase the clinical relevance of the present study, both patients with BPD as well as those with borderline personality features are included. For this study patients with borderline personality features are included if they have three or more of the DSM-IV-TR diagnostic criteria, with the additional requirement that these include both impulsivity and anger bursts, since STEPPS training is specifically aimed at improving skills to regulate these symptoms.

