### Statistical analyses

Differences in baseline data between the STEPPS condition and TAU condition are analyzed by t-test for continuous variables (demographic characteristics and scores on the outcome variables). Differences in utilizing mental healthcare between both groups will also be analysed by t-test. Categorical variables will be analyzed by chi-square. Both groups will be compared to an average number of symptomatic days/year, differentiated according to severity (LCM).

Linear Mixed Model (LMM) under the missing at random (MAR) will be used to analyze questionnaires data: the severity of manic and depressive symptoms (IDS-SR & YMRS), severity and course of borderline symptoms (BPDC-47 & PAI-BOR), psychological and somatic distress (BSI total score) and quality of life (OQ-45 & WHOQol Bref).

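### STEPPS is given in groups, but the 64 per arm allows for no clustering by STEPPS group and the analysis section does not mention it, so the stated 80% power holds only at a group ICC of zero or one trial patient per group

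*Protocol article*

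**What the plan says.** The Background section describes STEPPS as a group skills treatment of 20 weekly sessions: "Two trainers deliver the training. The group size is 8–12 patients". The Intervention section adds it to individual TAU. The control arm receives TAU only.

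The Sample size section gives "Inclusion of 64 patients for each group" for 80% power, 5% alpha and a Cohen's d of 0.50. The only inflation is for attrition: "Assuming a loss of 10% 140 patients will be enrolled". Directly afterwards it says "Patients will participate in STEPPS groups that are normally organized in the participating centers", and explains that these are routine groups, not set up for the trial, which trial patients share with patients whose primary diagnosis is BPD.

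The Statistical analyses section compares healthcare use between the arms by t-test and categorical variables by chi-square. For the Life Chart comparison of symptomatic days it names no test. For the questionnaires it says "Linear Mixed Model (LMM) under the missing at random (MAR) will be used to analyze questionnaires data" and gives no random effects. STEPPS group, trainer and centre do not appear in this section, although the Design section calls the trial multicentre.

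**The concern.** Members of one STEPPS group share two trainers, 20 sessions and one another, so their outcomes may be positively correlated. TAU-only patients have no comparable grouping. Such correlation raises the variance of the STEPPS mean and leaves the TAU mean as it was.

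This matters for two things. One is the planned size: a calculation for independent patients overstates the power of an analysis that handles the groups properly. The other is the analysis: a test that ignores the groups has a standard error that is too small, and could credit STEPPS with what is partly the effect of particular groups or trainers. There is also a practical risk. If group membership is not recorded during the trial, the suitable analysis may be impossible afterwards.

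**Working it through.** **Inputs from the protocol article.** 64 per arm analysed, d = 0.50 (SD taken as 1), 80% power and 5% alpha (Sample size); whole-group size 8–12 (Background). Sidedness is not stated, but two-sided reproduces the figure; a one-sided test would need only 50 per arm.

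**Assumptions.** The article gives neither the ICC nor m, the number of trial patients per STEPPS group. Groups are taken as equal in size, and total variance as equal in the two arms.

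**Step 1: reproduce the plan's figure.** For independent patients the noncentrality is 0.5 × √(64/2) = 2.828. The noncentral t with 126 df gives power of 80.1% at 64 per arm and 79.5% at 63. So 64 is the smallest number that reaches 80%, with a design effect of exactly 1. Enrolment holds no reserve: 140 × 0.9 = 126, against 2 × 64 = 128.

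**Step 2: allow for clustering in the STEPPS arm only.**
- Design effect in that arm: D = 1 + (m − 1) × ICC.
- Variance of the difference: D/64 + 1/64, which is V = (D + 1)/2 times the independent-patients value.
- Noncentrality: 0.5 × √(64/(2V)).
- Number per arm to restore 80%: 64 × V, rounded up.
- Type I error of a test that ignores groups: 2 × [1 − Φ(1.96/√V)].

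| m | ICC | D | V | True SE / naive SE | Noncentrality | Power if groups modelled (126 df) | n per arm for 80% | Type I error if groups ignored |
|---|---|---|---|---|---|---|---|---|
| 1 | any | 1.00 | 1.000 | 1.000 | 2.828 | 80.1% | 64 | 5.0% |
| 2 | 0.02 | 1.02 | 1.010 | 1.005 | 2.814 | 79.8% | 65 | 5.1% |
| 4 | 0.05 | 1.15 | 1.075 | 1.037 | 2.728 | 77.3% | 69 | 5.9% |
| 8 | 0.05 | 1.35 | 1.175 | 1.084 | 2.609 | 73.5% | 76 | 7.1% |

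Over the wider grid of m = 3 to 12 and ICC 0.02 to 0.10, power runs from 79.4% down to 61.6%. The low end needs groups of 12 made up entirely of trial patients.

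**Step 3: few groups.** The 126 df are slightly generous when there are few groups. With k = 64/m groups, a = D/64 and b = 1/64, the Satterthwaite df are (a + b)² / [a²/(k − 1) + b²/63]. This gives about 83, 44 and 20 df for the three clustered rows, and power of 79.4%, 76.1% and 69.9%.

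The last two columns describe different consequences. Reduced power at a valid 5% level belongs to an analysis that models groups; inflated type I error belongs to one that ignores them.

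**The case against.** Four stronger readings are tempting, and the article does not support them.

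- **That every planned analysis treats patients as independent.** The random effects of the mixed model are not given and no test is named for the Life Chart comparison. A condensed article may leave both to the analysis plan. The one outcome comparison expressly given an independence-assuming test is healthcare use, a secondary outcome.
- **That the cluster size is 8–12.** That is the whole group, and the Sample size section says groups are shared with non-trial patients. What counts is trial patients per group, which is probably smaller. At m = 2 to 4 and ICC 0.02 to 0.05, power is 77.3% to 79.8% and type I error with groups ignored is 5.1% to 5.9%. The loss is then at most about 3 points.
- **That the trial suffers both low power and inflated type I error.** One analysis does not have both sets of figures. If groups are ignored, the chance of rejection at d = 0.50 is about 79.3% (m = 4, ICC 0.05) or 78.3% (m = 8, ICC 0.05), not 77.3% or 73.5%.
- **That every outcome is affected.** This would need a positive ICC for each outcome, and the article gives none.

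It can also be said that repeated measures or baseline adjustment in the mixed model may win back some power. That is fair, but neither corrects a standard error that ignores groups.

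These objections limit the size and scope of the point and do not remove it. Enrolment is fixed in this article by a calculation with no allowance for clustering, right beside the description of the groups.

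**Conclusion.** The point stands in a limited form. The design is partially nested and the sample size treats patients as independent, so the stated 80% is right only at a group ICC of zero or with one trial patient per STEPPS group. The healthcare-use t-test assumes independence. Whether the mixed model does so cannot be told from the article.

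The size depends on two quantities that the article does not give. For the mixed groups it describes, the loss may be well under one point (79.8% at m = 2, ICC 0.02) or about three points (77.3% at m = 4, ICC 0.05). The 73.5% at m = 8 is an upper-range case that needs groups made up mostly or wholly of trial patients. This should be fixed because the remedy is cheap and group membership must be recorded in time, but on these figures it does not undermine the trial.

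**What to change.** 1. Record the STEPPS group attended by each patient randomised to STEPPS.
2. Analyse the outcomes with a partially nested mixed model: a random STEPPS-group effect in the STEPPS arm only, a centre term, and Satterthwaite or Kenward-Roger degrees of freedom. If the full analysis plan already has this, say so.
3. Use the same structure in place of the t-test for healthcare use.
4. Restate the power as 80% only at ICC = 0. Give the expected number of trial patients per group, an assumed ICC, and power over a range of both, as in the table.

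The cost is one extra data field and some wording in the analysis and sample size sections. Intervals become slightly wider and the stated power lower. No extra patients are needed for this change; it makes the power statement honest but does not restore 80%.

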### Statistical analyses

Differences in baseline data between the STEPPS condition and TAU condition are analyzed by t-test for continuous variables (demographic characteristics and scores on the outcome variables). Differences in utilizing mental healthcare between both groups will also be analysed by t-test. Categorical variables will be analyzed by chi-square. Both groups will be compared to an average number of symptomatic days/year, differentiated according to severity (LCM).

Linear Mixed Model (LMM) under the missing at random (MAR) will be used to analyze questionnaires data: the severity of manic and depressive symptoms (IDS-SR & YMRS), severity and course of borderline symptoms (BPDC-47 & PAI-BOR), psychological and somatic distress (BSI total score) and quality of life (OQ-45 & WHOQol Bref).

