[25] for severity of manic symptoms. The burden of borderline symptoms will be assessed with the *Borderline Personality Disorder Checklist* (BPDC-47)
[33] and *Personality Assessment Inventory – Borderline Features (PAI-BOR)*[34]*.* Quality of life will be measured with the *Outcome Questionnaire* (OQ-45)
[35] and *World Health Organization Quality of Life short version* (WHOQol Bref)
[36]. Patient empowerment will be assessed with the *Patient Activation Measure* (PAM)
[37]. To assess the illness course over the past year, all participants will complete the retrospective version of the LCM. Figure 
3 shows a summary of measures of study 2.

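### The plan tests baseline differences between randomised arms, which is uninformative, and states no baseline term for the LCM comparison although a past-year LCM is collected from everyone

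*Protocol article*

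**What the plan says.** All statements are in the protocol article.

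- **Baseline (Statistical analyses).** "Differences in baseline data between the STEPPS condition and TAU condition are analyzed by t-test for continuous variables". The parenthesis that follows covers demographic characteristics and the outcome scores. A later sentence assigns chi-square to categorical variables without saying whether that means baseline variables.
- **LCM outcome (Statistical analyses).** "Both groups will be compared to an average number of symptomatic days/year", split by severity. No test, model or covariate is named. The Abstract makes the recurrence of manic and depressive episodes a primary outcome, and Procedure and outcome measures uses the prospective LCM to follow the course of bipolar disorder.
- **Past-year LCM (Procedure and outcome measures).** "To assess the illness course over the past year, all participants will complete the retrospective version of the LCM". No analytic use is stated for it.
- **Questionnaires (Statistical analyses).** These go into a linear mixed model. All outcome measures are taken at T0, T1, T2 and T3, but the text does not say how T0 enters the model.
- **Sample size.** "Inclusion of 64 patients for each group", for 80% power at 5% alpha and d = 0.50.

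**The concern.** There are two linked points.

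First, a significance test between randomised arms at baseline asks whether the difference could be due to chance. If allocation was sound, it was. A small p-value does not show that the variable affects the outcome, and a large one does not show that an imbalance is harmless. With many scales tested, some nominally significant differences are to be expected, and the article gives no rule for what would follow from them.

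Second, baseline information is useful for adjustment. Patients with recurrent mood disorder can be expected to differ in their prior course. If past-year symptomatic days predict follow-up days, part of the outcome variance can be removed. The past-year value is collected from every participant, but the stated LCM comparison does not use it. What is at stake is precision on a primary outcome, not validity.

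**Working it through.** **Inputs.** From Sample size: 64 per group, alpha 5%, power 80%, d = 0.50. Sidedness is not stated. The correlation r between past-year retrospective and follow-up prospective symptomatic days is not in the documents, so r = 0.2 to 0.6 is assumed. Sample size ties d = 0.50 to no particular outcome; here it is applied to the LCM comparison.

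**1. The plan's own figure.** For a two-sample t-test the noncentrality is d × √(n/2) with 2n − 2 degrees of freedom. At n = 64 this is 0.50 × √32 = 2.83 with 126 df, and two-sided power is 0.801. At n = 63 power is 0.795. A one-sided test would need only 50 per arm (normal approximation). So 64 is the exact answer for a two-sided, unadjusted comparison, and the calculation takes no credit for baseline information.

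**2. Baseline tests.** Procedure and outcome measures names ten instruments: BPDSI, BSI, IDS-SR, YMRS, BPDC-47, PAI-BOR, OQ-45, WHOQol Bref, PAM and LCM. If each gave one independent test at 5%, the chance of at least one p < 0.05 under perfect randomisation would be 1 − 0.95^10 = 0.40. The scales are correlated, so this figure is only illustrative.

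**3. Size of chance imbalance.** At 64 per arm the SD of a standardised baseline difference is √(2/64) = 0.18, so the 95% range is about ±0.35 SD. At r = 0.5 this shifts an unadjusted estimate by up to 0.5 × 0.35 ≈ 0.17 SD, about a third of d = 0.50. The unadjusted standard error already includes this variation.

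**4. Gain from adjustment.** Analysis of covariance multiplies the residual variance by 1 − r². The noncentrality becomes d × √(n/2) / √(1 − r²) with 2n − 3 df. For r = 0.5 it is 2.83 / √0.75 = 3.27, which gives power 0.90.

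| r (assumed) | 1 − r² | Variance reduction | Power at 64 per arm | n per arm matching 64 unadjusted |
|---|---|---|---|---|
| 0 | 1.00 | 0% | 0.80 | 64 |
| 0.2 | 0.96 | 4% | 0.82 | 62 |
| 0.3 | 0.91 | 9% | 0.84 | 59 |
| 0.4 | 0.84 | 16% | 0.86 | 54 |
| 0.5 | 0.75 | 25% | 0.90 | 48 |
| 0.6 | 0.64 | 36% | 0.94 | 41 |

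The last column is 64 × (1 − r²), rounded up.

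**The case against.** The best defence is that most of this is silence in a condensed article. The LCM analysis is one sentence, and covariates are commonly left to a full protocol or analysis plan that is not shown. A reader might infer that the baseline tests are meant to replace adjustment, or that the past-year LCM is deliberately set aside. The article says neither. It does not even name a test for symptomatic days, and the planned baseline comparison of outcome scores could include the past-year LCM. That part of the defence stands.

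A reader might also extend the point to the questionnaires. The text does not support this: a mixed model on data from T0 to T3 may already use T0, as a repeated measure or as a covariate.

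Nor are the two LCM measures the same quantity. One is recalled over the past year, while the other is recorded prospectively with follow-up to 18 months. Their correlation may be low, and at r = 0.2 the gain is about 2 percentage points of power. The sentence on the retrospective LCM does not itself give its timing. Baseline is the natural reading, but the measurement schedule is in a figure that is not shown.

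Finally, chance imbalance does not bias a randomised comparison. The baseline tests alter no treatment estimate either, since nothing says covariates will be chosen from them.

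These arguments limit the wording and the size of the point. They do not remove the baseline tests, which are an explicit choice. They also do not change the fact that the LCM comparison, as described, has no baseline term while a suitable value is already being collected.

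**Conclusion.** The point holds in a limited form. The baseline significance tests are stated and uninformative. For the LCM outcome, adjusting for the past-year value would improve on the comparison as described, at no cost in data.

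The gain is in the same direction for any meaningful correlation, but its size rests on an assumed r. For r from 0.2 to 0.6, power goes from 0.80 to between 0.82 and 0.94. These figures also assume an approximately linear relation and d = 0.50 on the unadjusted scale.

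A reader might infer that the trial is underpowered, or that its 64 per arm would certainly be worth 70 to 100 after adjustment. The first does not follow, because 64 per group gives the planned power without adjustment. The second is 64 / (1 − r²) at r = 0.3 and r = 0.6, and the documents support neither value. What would be lost is an optional gain in precision; the unadjusted comparison remains valid.

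**What to change.** - Replace the baseline tests with a descriptive table by arm (means and SDs or medians and quartiles; counts and percentages), without p-values. If the chi-square sentence refers to baseline variables, treat it in the same way.
- Name a model for symptomatic days per year. Prespecify the matching past-year retrospective LCM value, for the same severity category, as a covariate.
- Confirm that the retrospective LCM is completed at T0, before the allocation is known, so that recall cannot depend on arm.
- As a clarification only, add a phrase saying how T0 enters the questionnaire mixed models.

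The cost is a few sentences of analysis text. No extra patients or assessments are needed, and the sample size can stay as it is.

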## Abstract

**Background:**

Bipolar disorder (BD) and borderline personality disorder (BPD) both are severe and chronic psychiatric disorders. Both disorders have overlapping symptoms, and current research shows that the presence of a BPD has an adverse effect on the course of BD. The limited research available shows an unfavorable illness course, a worse prognosis and response to medication, longer treatment duration, more frequent psychiatric admissions, higher drop-out, increased risk of substance abuse, increased risk of suicide, and more impairment of social and occupational functioning. However, there is no research available on the effect of specific psychotherapeutic treatment for this patients.

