### Objectives

#### Study part 1

Primary objective:

• To investigate the prevalence of borderline personality features in outpatients with BD.

#### Study part 2

Primary objectives:

• To investigate the effectiveness of STEPPS added to TAU on the symptoms and course of BD in patients with BD and comorbid borderline personality features.

• To investigate whether addition of STEPPS to TAU is differently associated with a decrease of frequency and severity of manic, hypomanic or depressive episodes.

• To investigate the effectiveness of STEPPS added to TAU on the symptoms, course and burden of borderline personality features.

Secondary objectives:

• To investigate whether addition of STEPPS to TAU is associated with an increase of quality of life.

• To investigate whether addition of STEPPS to TAU is associated with a decrease of utilizing mental healthcare.

• To investigate whether addition of STEPPS to TAU is associated with a decrease of psychiatric symptoms not primarily related to BD or borderline personality features.

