### Procedure and outcome measures

Study part 1: The aim of study part 1 is to investigate the prevalence of borderline personality features in patients with a diagnosis of BD. After informed consent all patients with the diagnosis of BD are asked to complete the *Personality Disorder Questionnaire-4+* (PDQ-4+
[26], Dutch translation
[27]) to screen for the prevalence of BPD. After screening all patients who score positively on the presence of BPD will be asked to participate in a *Structured Clinical Interview for DSM-IV Personality Disorders* (SCID-II)
[28]; Dutch translation
[29]. The SCID-II will start with modules concerning BPD. In case of the presence of three BPD symptoms, including both impulsivity and anger bursts, the interview will be continued with modules of other personality disorders to explore further axis-II comorbidity. In case of presence of less than three BPD symptoms (including both impulsivity and anger burst) the interview will be terminated. The diagnosis of BD (inclusive subtype I, II & NOS) will be verified with modules A (depression), C (suicidality) and D (mania) of the MINI-Plus
[23]. Modules K & L will be completed to determine substance abuse, and module M part I & II will be completed to exclude schizoaffective disorder. In patients who were previously assessed with the MINI-Plus, a re-test will be completed only if the information is older than 2 years.

Study part 2: After inclusion into the trial patients are randomly assigned either to the STEPPS added to treatment as usual (TAU) for bipolar disorder or the control group receiving TAU for BD only. Patients in the intervention group will be assessed on all outcome measures at baseline (T0), at the end of the intervention (T1) and 12 (T2) and 18 (T3) months after start of treatment. Patients in the TAU control group will be assessed at baseline and at corresponding intervals. The course of BD and utilization of mental healthcare (number of consultations) is measured with the prospective version of the *Life Chart Methodology* (LCM)
[30]. At baseline all patients will be assessed with the *Borderline Personality Severity Index* (BPDSI) for severity of borderline symptoms
[31], the *Brief Symptom Inventory* (BSI)
[32] for severity of general psychological symptoms, the *Inventory of Depressive Symptomatology* (IDS-SR)
[24] for severity of depressive symptoms, and the *Young Mania Rating Scale* (YMRS)

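### Care use is a consultation count compared by t-test with no time base, so unequal charting time between arms could bias it in either direction

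*Protocol article*

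**What the plan says.** Under Objectives (study part 2), a secondary aim is to find out whether adding STEPPS to TAU is "associated with a decrease of utilizing mental healthcare". Under Procedure and outcome measures, "utilization of mental healthcare (number of consultations) is measured with the prospective version" of the Life Chart Methodology (LCM), with the last assessment 18 months after the start of treatment. Under Statistical analyses, the only method named for this outcome is: "Differences in utilizing mental healthcare between both groups will also be analysed by t-test".

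Two neighbouring statements in that section are handled differently:

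- The mood outcome from the same life chart is an average number of symptomatic days per year, so it carries a time base.
- "Linear Mixed Model (LMM) under the missing at random (MAR) will be used to analyze questionnaires data". The list that follows covers mood symptoms, borderline symptoms, general distress and quality of life. Care use is not in it.

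On the pre-trial period, all outcome measures are said to be assessed at T0, and every participant completes a retrospective life chart for the past year. That chart is described as covering illness course. A pre-trial number of consultations is not named, and no baseline value enters the care-use test.

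**The concern.** A number of consultations accrues with time. At a constant rate, a patient who charts for 6 of 18 months records 6/18, or one third, of the consultations of an identical patient who charts throughout. A t-test on counts cannot tell a patient who used little care from one who was observed briefly.

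Of the follow-up outcomes with a named between-group method, care use is the one with neither a time base nor a missing-data approach. At stake is the secondary objective on care use. If charting time differs between arms, the comparison mixes a difference in care with a difference in observation. It could suggest a decrease that did not occur or hide one that did.

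**Working it through.** **The plan's own figures.** No figure is given for care use. The general sample size reproduces: for d = 0.50, two-sided 5% and 80% power, the exact two-sample t-test needs 63.8, so 64 per group (power 0.801). Allowing for 10% loss, 128/0.90 = 142.2, so 143. The stated 140 is close: 140 × 0.90 = 126, or 63 per group, with power 0.795. The 10% is an overall figure, not split by arm.

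**Bias from unequal observation.** Let d1 and d0 be the proportions who stop charting early under STEPPS and TAU. Assume that stopping times are uniform over follow-up, the consultation rate is constant, the true rates are equal, and partial counts are analysed unscaled. An early stopper is observed for half of follow-up on average, so the mean observed fraction in an arm is (1 - d) + d/2 = 1 - d/2. The expected ratio of raw counts is

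(1 - d1/2) / (1 - d0/2).

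| Loss, STEPPS / TAU | Calculation | Bias in STEPPS count |
|---|---|---|
| 10% / 10% | 0.95 / 0.95 | 0% |
| 15% / 5% | 0.925 / 0.975 = 0.949 | -5.1% |
| 20% / 0% | 0.90 / 1.00 = 0.900 | -10.0% |
| 30% / 10% | 0.85 / 0.95 = 0.895 | -10.5% |
| 10% / 30% | 0.95 / 0.85 = 1.118 | +11.8% |

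The first three rows average 10% loss, the protocol's own figure. The last two average 20%.

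**Effect on the t-test.** This was simulated with 70 per arm, 5,000 trials per setting and gamma-Poisson counts with equal true rates. The mean of 30 consultations over 18 months and the gamma shapes 1 to 4 are assumptions, not taken from the document. The count SD is √(30 + 900/shape), which is 30.5, 21.9 and 16.0 for shapes 1, 2 and 4.

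| Loss, STEPPS / TAU | Two-sided 5% rejection, shapes 1 to 4 | Direction |
|---|---|---|
| 10% / 10% | 4.7 to 5.2% | none |
| 15% / 5% | 5.7 to 8.2% | mostly favours STEPPS |
| 20% / 0% | 8.9 to 19.3% | nearly all favours STEPPS |
| 30% / 10% | 9.3 to 19.4% | nearly all favours STEPPS |
| 10% / 30% | 10.0 to 19.8% | nearly all against STEPPS |

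Hand check at 30%/10%, shape 2: the means are 30 × 0.85 = 25.5 and 30 × 0.95 = 28.5, a difference of -3.0. The standard error is about 21.9 × √(2/70) = 3.7. The shift is 0.81 standard errors, which implies roughly 13% rejection. The simulation gave 12.3%.

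**With a time base.** Total consultations divided by total observed time gave rate ratios of 0.995 to 1.007 in every no-effect setting, so the artefact disappears.

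**Equal loss.** With a true 20% reduction (shape 2) and equal loss of 0%, 10% and 30%, the count ratio stays at 0.80. Power falls from 43% to 39% to 34%.

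**What the replacement gains.** A second simulation assumed a mean of 24 consultations, lognormal patient rates and 70 per arm. With a true rate ratio of 0.75 and 15% stopping in each arm, power was 44.7% by t-test and 50.4% with an observed-time offset. It was 62.9% when a prior-year count (correlation about 0.55) was added. With 10% stopping under STEPPS and 25% under TAU, the t-test fell to 23.5%, against 60.1% for offset plus prior count. Under equal rates the offset model rejected 5.6 to 6.8% of the time, slightly above nominal, so part of the small gain from the offset alone may reflect that.

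**The case against.** **Unscaled partial counts are not stated.** A t-test is also compatible with counts scaled to time or with complete follow-up only, and a condensed article may leave the choice to a fuller plan. This stands, and the bias figures are conditional on it. It does not rescue the named method. Scaling to time is the correction proposed here and should be written down. Completers only would drop partial charts and select patients, unlike the mixed model used for the questionnaires.

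**The direction is not known.** A reader might infer that drop-out will appear as the hoped-for decrease in care. The document does not support that: it requires STEPPS to lose more observation time. The abstract does list "longer treatment duration, more frequent psychiatric admissions, higher drop-out", but as consequences of having BPD alongside BD. Every randomised patient, in both arms, has BPD or its features, so the statement does not predict a difference between arms. Only STEPPS adds 20 weekly sessions, which makes unequal loss plausible without showing which way it goes.

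**The size is modest at the planned loss.** At 10% in each arm there is no bias in the ratio, and a 15%/5% split moves the mean by about 5%. The 30%/10% and 10%/30% cases are stress tests beyond the stated 10%.

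**A pre-trial count may exist.** A reader might infer that none is collected. That is too strong, given the T0 assessment of all outcome measures and the retrospective chart. What is absent is any named pre-trial consultation count or its use in the test. Randomisation also makes an unadjusted comparison valid, so the covariate is a matter of precision.

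**Other uncertainties.** Whether STEPPS sessions count as consultations is not stated. If they do, up to 20 are added in one arm, far more than the observation-time effect, and an offset does not address that. The t-test sentence also directly follows the baseline comparisons, so its time window is unclear. It is nevertheless the only analysis given for this objective.

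**Conclusion.** The point holds in a limited form. The plan names a t-test for a count that accrues with observation time and fixes no time base, observation-time adjustment or baseline term, although the outcome next to it from the same instrument is per year.

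If incomplete charts are counted as they stand, unequal charting time biases the comparison in either direction. Under uniform stopping the bias is about 5% at a 15%/5% split and 10 to 12% at more unequal splits. Equal loss leaves the ratio unbiased and costs some power. The percentage biases need only the assumptions of uniform stopping and a constant rate. The rejection rates also depend on an assumed mean and spread that the document does not give.

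This affects one secondary objective. It is worth correcting because the remedy is cheap and is best fixed before the data are seen. It does not touch the primary outcomes.

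**What to change.** In Statistical analyses, replace the t-test sentence for care use with wording along these lines:

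*The number of consultations from the start of treatment (or the corresponding date under TAU) to 18 months will be compared between groups with a log-link count model (negative binomial, or Poisson with robust standard errors), with the logarithm of observed charting time as offset. All patients with any charted time will be included. If a pre-trial number of consultations is recorded at T0 or with the retrospective LCM, it will be added as a covariate. The rate ratio with its 95% CI will be reported.*

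The same text should define how observed charting time is determined when a chart is interrupted or ends early.

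The cost is slightly more analysis work, plus an assumption that the consultation rate after charting stops resembles the observed rate. That assumption should be stated. Extracting appointment records from the clinics could strengthen the data, but it is a new source that the document does not describe. It is optional and not part of this fix.
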